## List of abbreviations

|           |                                                     |
|-----------|-----------------------------------------------------|
| ACVE      | Adverse Cardiovascular Events                       |
| AE        | Adverse Event                                       |
| ABPM      | Ambulatory Blood Pressure Monitor                   |
| AIS       | American Spinal Injury Association Impairment Scale |
| ARM       | Anorectal Manometry                                 |
| ADFSCI    | Autonomic Dysfunctions following SCI                |
| AD        | Autonomic Dysreflexia                               |
| BP        | Blood Pressure                                      |
| BSCC      | Blusson Spinal Cord Centre                          |
| CIC       | Clean Intermittent Catheterization                  |
| DSD       | Detrusor Sphincter Dyssynergia                      |
| EMG       | Electromyography                                    |
| EUS       | External Urethral Sphincter                         |
| FSFI      | Female Sexual Function Index                        |
| GCP       | Good Clinical Practice                              |
| GI        | Gastrointestinal                                    |
| HR-QoL    | Health-Related Quality of Life                      |
| HR        | Heart Rate                                          |
| I-QoL     | Incontinence-QoL                                    |
| ICF       | Informed Consent Form                               |
| ICORD     | International Collaboration on Repair Discoveries   |
| ICH       | International Council for Harmonisation             |
| IIEF-15   | International Index of Erectile Function            |
| LUT       | Lower Urinary Tract                                 |
| NBSS      | Neurogenic Bladder Symptom Score                    |
| NBD Score | Neurogenic Bowel Dysfunction Score                  |
| NDO       | Neurogenic Detrusor Overactivity                    |
| PHQ-9     | Patient Health Questionnaire                        |
| QoL       | Quality of Life                                     |
| SCI       | Spinal Cord Injury                                  |
| TNFBM     | Time needed for Bowel Movement                      |
| TCSCS     | Transcutaneous Spinal Cord Stimulation              |
| TEAE      | Treatment Emergent Adverse Events                   |
| UDS       | Urodynamics                                         |
| WIS       | Wexner Incontinence Score                           |

## Background literature review

In addition to devastating paralysis, individuals with SCI suffer from a myriad of less visible autonomic dysfunctions. Restoration of autonomic functions, specifically lower urinary tract (LUT), bowel and sexual functions, are rated among the highest priorities for recovery in individuals with SCI. Multiple studies have highlighted the staggering discrepancies between the priorities of people with SCI and the focus of research efforts to date. Despite this, the vast majority of research is focused on overt disabilities following SCI (e.g. motor paralysis), whereas more devastating 'invisible' disabilities such as LUT, bowel and sexual dysfunctions, which are of higher priority than walking, are unfortunately understudied.

SCI disrupts crucial crosstalk between the spinal autonomic nervous system and supraspinal control centres. Therefore, contrary to the general perception, SCI results in not only motor paralysis but also in a pernicious cascade of severe impairments in vital autonomic functions such as LUT, bowel and sexual control. Moreover, impairments in these functions lead to life-threatening cardiovascular consequences e.g. extreme hypertensive episodes of autonomic dysreflexia. These dysfunctions affect all aspects of life post-SCI and are the most important determinants of dignity, autonomy, health and survival of the affected individual.

Bladder function [clinically referred to as LUT function]: The human LUT comprises two functional components: the urinary bladder (*detrusor*) as well as the unit of the bladder neck, urethra, and urethral sphincter, which are responsible for low pressure continent storage of urine and periodical, self-determined, complete release of the stored urine (*voiding*). To properly execute both functional components, the LUT relies on an intact nervous system with coordinated control by cortical and spinal (thoracolumbar and sacral) centres. Impairment or the loss of LUT control following SCI inevitably results in LUT dysfunction and consequently reduces HRQOL. Failure in urine storage (due to involuntary detrusor contraction and inability to voluntarily activate the external urethral sphincter (EUS) and voiding (due to the inability to voluntarily initiate) combined with detrusor-sphincter-dyssynergia DSD, a condition where the detrusor and the external urethral sphincter contract at the same time, results in high intravesical pressure and inefficient voiding with a significant post-void residual volume. This pathologic, high-pressure situation jeopardizes the entire urinary tract long-term as it leads to vesico-ureteral-renal reflux, urinary tract infections, bladder stone formation, and impaired renal function – ultimately leading to significant disease burden and poorer HRQOL. The fundamental cause underlying impairment of LUT function post SCI is loss of supraspinal control and disruption of crosstalk between the somatic and autonomic nervous systems. The resulting condition, termed neurogenic LUT dysfunction, impacts over 90% of individuals with SCI.

Bowel function is also significantly compromised after SCI, presenting as constipation, impaired colonic motility and loss of volitional control resulting in episodes of faecal incontinence - predisposing an individual to increased risk of long-term complications. These impairments, coupled with impaired mobility and hand dexterity make bowel management a major life-altering problem. Normal bowel function, i.e. focusing on the lower gastrointestinal (GI) tract, is regulated by a fine balance between somatic and autonomic (sympathetic, parasympathetic and enteric) control. Moreover, voluntary defaecation relies on supraspinal control. Despite the intricate crosstalk between multiple layers of neural control governing bowel function, it is the somatic and autonomic components of the central nervous system that regulate peristalsis/defaecation (i.e. another major concern in individuals with SCI). In most cases of SCI (i.e. cervical or high-thoracic), the proximal colon has intact parasympathetic but not sympathetic supraspinal control, while the distal colon loses supraspinal autonomic control altogether. Over 98% of individuals with SCI report at least one bowel issue e.g. Time needed for bowel

movement (TNFBM) lasting up to two hours and over 60% report that bowel dysfunction adversely impacts HRQOL.

The LUT and bowel share spinal circuitry and rely on a low-pressure system to store urine or arrange stool transportation. For elimination (i.e. voiding and defaecation), the LUT (*bladder*) and bowel (*rectum*) increase organ-specific, intravesical and intraabdominal pressures respectively, while reducing the outlet obstruction to a minimum, i.e. by relaxing their respective external (*urethral and anal*) sphincters. As with the LUT, continuous elevated pressure in the lower gastrointestinal (GI) tract places affected individuals at increased risk for haemorrhoids, anal fissures, diverticular disease, rectal bleeding, and rectal prolapse (a condition in which the rectal wall pushes out through the anus). Therefore, it is paramount to restore LUT and bowel function with respect to the intravesical and abdominal pressure (i.e. low during storage and appropriate increase during elimination). Thus, in order to assess LUT and bowel function, this proposal will utilize well-established and robust procedures i.e. urodynamics (UDS), along with external anal sphincter/pelvic floor surface electromyography (EAS/PF) for LUT function, and Anorectal Manometry (ARM) for lower GI function.

Severe impairments in sexual function following SCI include erectile dysfunction, ejaculatory disorders/anejaculation in men and reduced vaginal lubrication in women, with both sexes experiencing orgasmic difficulties or anorgasmia as well as alterations in sexual drive and sexual satisfaction. Obtaining and maintaining an erection that is sufficient for satisfactory sexual performance and to achieve ejaculation and orgasm (for both pleasure and biological fatherhood) is therefore a major concern for men following SCI, with up to 89% experiencing erectile difficulties. Both men and women with SCI also experience compromised orgasmic ability, with a 75% and 43% incidence, respectively. Several systematic reviews of the literature identified sexual function as one of the most important priorities for individuals with SCI and improvements in sexual function is considered an instrumental aspect of successful rehabilitation. The World Health Organization recognizes sexual function as a fundamental right and targeted approaches that may provide improvements in these outcomes are of utmost priority for individuals with SCI.

Finally, it is important to recognize that life-threatening cardiovascular dysfunctions post-SCI are commonly associated with these autonomic dysfunctions. In fact, [name] laboratory has extensively demonstrated that severe hypertensive episodes of autonomic dysreflexia are frequently triggered by stimuli arising from LUT, bowel or sexual organs. Therefore, any intervention or stimulation applied below the level of SCI should also be evaluated for cardiovascular safety, as triggered autonomic dysreflexia could be associated with significant, life-altering ACVEs.

This study will use the TEScON device is a non-invasive electrical device provides transcutaneous spinal cord stimulation for the treatment for patients with cardiovascular dysfunction, neurogenic lower urinary tract dysfunction and neurogenic bowel dysfunction, sexual dysfunction and sensorimotor impairments following spinal cord injury. Transcutaneous stimulation is applied to the spinal cord by electrodes connected to a battery-powered source which activates the nerves associated with autonomic function.

## Purpose

The purpose of this project is to assess the safety and efficacy of non-invasive transcutaneous spinal cord stimulation (TCSCS) in promoting recovery of LUT, bowel and sexual function in individuals with SCI.

## Objectives, Hypotheses and Outcomes

**Objective 1:** To establish specific spatiotemporal activation maps for TCSCS at various spinal cord segments known to be involved in LUT and bowel control.

**Hypothesis 1:** In light of recent findings on the efficacy of spinal cord stimulation to improve bowel and LUT function, the optimal setting for motor responses (i.e. mapping) will be revealed during TCSCS.

**Primary outcome 1:** An individualized TCSCS map (i.e. location and stimulation parameters) to elicit optimal skeletal muscle activation corresponding to spinal cord segments involved in LUT and bowel control

**Objective 2:** To test whether targeted short-term TCSCS is safe with respect to cardiovascular consequences (e.g. autonomic dysreflexia) and can repeatedly improve LUT and bowel functions in humans with chronic SCI.

**Objective 2A) LUT function (safety/efficacy):** To test whether targeted short-term TCSCS is safe and can induce detrusor contractions (*voiding function*) while relaxing the EUS, i.e. to avoid DSD and independently enhance EUS tone (*storage function*).

**Hypothesis 2A):** In light of recent findings demonstrating TCSCS improves LUT function, we hypothesize that short-term TCSCS will improve voiding and storage functions without ACVEs.

**Outcome 2A):** Changes from baseline in the following UDS parameters for bladder capacity/compliance:

- i. Volume at the first sensation
- ii. Intravesical pressure (Pves) at the first sensation
- iii. Volume at the leakage point
- iv. Pressure at the leakage point
- v. Maximum bladder volume
- vi. Pves at the maximum bladder volume

**Objective 2B) LUT function (repeatability of TCSCS to improve UDS parameters):** To test whether targeted short-term TCSCS will repeatedly improve UDS parameters across different stimulation sessions.

**Hypothesis 2B):** TCSCS will elicit reproducible improvements in UDS parameters without ACVEs.

**Outcome 2B):** Reproducibility of changes within urodynamic parameters during stimulation will be assessed during two consecutive urodynamic procedures. UDS parameters for bladder capacity/compliance:

- i. Volume at the first sensation
- ii. Pves at the first sensation

**Objective 2C) Bowel function (safety/efficacy):** To test whether targeted short-term TCSCS is safe and can result in an immediate increase in anorectal pressure.

**Hypothesis 2C):** TCSCS will increase anorectal pressure without adverse cardiovascular effects.

**Outcome 2C):** Mean increase in maximum resting pressure by at least 50%.

**Objective 3) LUT, bowel and sexual functions (long-term TCSCS):** To test whether targeted long-term TCSCS (6-week trial) is safe and can improve urinary and faecal continence in humans with chronic SCI.

**Objective 3A)** To test whether targeted long-term TCSCS can improve urinary and faecal continence.

**Hypothesis 3A)** Long-term TCSCS will improve urinary and faecal continence. These improvements will be greater in individuals who complete intensive long term TCSCS compared to individuals who complete moderate long term TCSCS.

**Outcome 3A):** Mean decrease in the frequency of urinary and faecal incontinence by at least 50%.

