### Statistical Plan

Statistical analysis on LUT, bowel and sexual function will be performed (n = 40 with SCI).

A sample size calculation was performed using G\*power, version 3.0.10, with power set at 0.8 and  $\alpha$  at 0.05. Data from participants that match our inclusion criteria (n = 5, level of lesion C5 – T10, motor-complete AIS, A or B) were used from a recent TCSCS study. A minimum sample of 26 participants is required to detect a significant change in voiding efficiency [voided volume / (voided volume + post-void residual volume)] with short-term TCSCS (stim-off =  $37.8 \pm 40.6\%$  vs. stim-on =  $58.2 \pm 39.4\%$ , effect size = 0.510). Presently, there are no long-term TCSCS data with LUT and bowel outcomes, consistent with those proposed in this protocol, to facilitate a meaningful power calculation. Therefore, given this is a pilot trial study, and in order to account for drop out with long-term TCSCS, we aim to investigate 40 individuals with SCI (n = 40, C5 – T6). Short-term TCSCS effects on UDS parameters (AIM 2A) as well as ARM testing (AIM 2C) with or without different stimulation configurations will be assessed using a repeated measures non-parametric analysis of variance (ANOVA), i.e. Kruskal–Wallis test. Data from the repeatability portion of the study (AIM 2A) will be assessed within (same session) and between (different sessions) visits (2 and 3) using a repeated measures non-parametric ANOVA. TNFBM will also be assessed using a repeated measures non-parametric ANOVA.

Long-term TCSCS: Differences in continuous variables for questionnaire data (NBSS, NBD Score, I-QoL, IIEF-15 or FSFI) in AIM 3 will be assessed using a two-way repeated measures [baseline, immediately post long term TCSCS as well as post-interventional follow up at 6 and 12 weeks] ANOVA comparing changes between moderate and intensive TCSCS. Furthermore, UDS testing as well as 'faecal continence severity' (baseline and end of TCSCS 6-week period) will be assessed using Wilcoxon signed-rank tests within

groups. A P-value less than 0.05 will be considered statistically significant. A complete thematic analysis will be performed to collect contextual qualitative data from the sexual health interview.

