### Urodynamics

Participants will undergo standard clinical procedures for UDS, including cystometry with water at 21°C and a filling rate of < 30 mL per minute through a 6F double lumen catheter with the participants in the supine position. Abdominal pressure will be measured with a 10F intrarectal balloon catheter. Pelvic floor electromyography will be recorded during cystometry with a surface electrode placed on the

perineum. Filling will be stopped when the participants report a sensation of fullness, at the moment of urine leakage, if blood pressure reaches levels of 180/110 mmHg, or per the request of the patient.

Following the standard clinical assessment UDS we will perform UDS with TCSCS. To assess the efficacy of short-term TCSCS' on LUT function, we will first prefill the bladder (i.e. 50-75% of cystometric capacity from the first UDS) without eliciting detrusor overactivity or autonomic dysreflexia. Then, TCSCS (as described above) will be delivered for 60 s each interspersed with 30 s rest (i.e. no stim) to optimize the configuration for each individual. Stimulation frequency and location will be guided by the results of the Baseline EMG Mapping of Spinal Cord Segments performed during visit 3.

TCSCS will be stopped when the participants report a sensation of fullness, at the moment of urine leakage, if blood pressure reaches levels of 180/110 mmHg, or per the request of the patient.

Urodynamics will be performed by a trained clinician (MD or RN) under the supervision of [name] (MD), who is a urologist.

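### Objective and Hypothesis 2A cover voiding and sphincter relaxation, but all six Outcome 2A parameters are capacity/compliance measures, and the sample size rests on voiding efficiency, which is not a listed outcome

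*Protocol*

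**What the plan says.** In the protocol's Objectives, Hypotheses and Outcomes section, Objective 2A asks whether stimulation "can induce detrusor contractions" with the external urethral sphincter relaxed, which is its voiding part, and separately whether it raises sphincter tone for storage. Avoiding detrusor-sphincter dyssynergia (DSD) is given as the reason for the relaxation. Hypothesis 2A follows: "short-term TCSCS will improve voiding and storage functions without ACVEs".

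Outcome 2A is introduced as "Changes from baseline in the following UDS parameters for bladder capacity/compliance". Its six items are bladder volume and intravesical pressure (Pves) at first sensation, volume and pressure at leakage, maximum bladder volume, and "Pves at the maximum bladder volume". Outcome 2B reuses the two first-sensation items.

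The Statistical Plan says that a minimum of 26 participants "is required to detect a significant change in voiding efficiency", defined there as voided volume divided by the sum of voided and residual volume. The analysis sentence for Aim 2A refers only to UDS parameters in general.

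The Urodynamics section describes a standard filling study with an intrarectal catheter for abdominal pressure, and states that "Pelvic floor electromyography will be recorded during cystometry". The run with stimulation starts from a bladder prefilled to 50-75% of cystometric capacity, followed by 60 s stimulation periods separated by 30 s rests. Leakage of urine is one of the events that ends stimulation.

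**The concern.** An objective, its hypothesis, its outcome and the variable used for sample size should describe the same thing. Here they do not. The objective and hypothesis have a voiding part (detrusor contraction with a relaxed sphincter) and a storage part, while the outcome list names only filling-phase measures. The sample size is built on a voiding measure that the outcome list omits.

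Two things are at stake. First, a favourable change in a storage parameter could be reported as support for Hypothesis 2A as a whole, although voiding and sphincter relaxation were never named as outcomes. Second, a reader who sees 80% power and 26 participants will assume that this describes the Outcome 2A comparisons, which it does not.

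**Working it through.** **Step 1: set the claims against the outcomes.**

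| Part of Objective/Hypothesis 2A | Outcome 2A parameter that measures it |
|---|---|
| Detrusor contraction (voiding) | none named |
| Sphincter relaxation, no DSD | none named |
| Storage | volume and Pves at first sensation; volume and pressure at leakage; maximum volume and Pves at that volume |

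None of the six is voided volume, residual volume, voiding efficiency, detrusor pressure during a contraction, or sphincter or pelvic-floor EMG.

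**Step 2: look for a repair elsewhere in the protocol.** Outcome 2B repeats two of the same filling measures. The Neurogenic Bladder Symptom Score has a storage and voiding domain, but it is a questionnaire given at baseline and after the six-week course, so it belongs to Aim 3. The background review names surface EMG alongside urodynamics as a means of assessing urinary function, but no outcome uses it.

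**Step 3: reproduce the sample size.** Inputs from the Statistical Plan: stimulation off 37.8 ± 40.6%, stimulation on 58.2 ± 39.4%, effect size 0.510, power 0.8, alpha 0.05.

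- Difference: 58.2 − 37.8 = 20.4.
- Averaged SD: √[(40.6² + 39.4²)/2] = √[(1648.36 + 1552.36)/2] = √1600.36 = 40.00.
- Effect size: 20.4/40.00 = 0.510, as stated.
- Used as a paired effect size, 0.510 implies a within-person correlation of about 0.5. The SD of the difference is then √(40.6² + 39.4² − 2 × 0.5 × 40.6 × 39.4) = 40.01, and 20.4/40.01 = 0.510. The protocol does not state a correlation. At 0.3 the paired effect size would be 0.431, and at 0.7 it would be 0.658.
- Exact paired t-test at 0.510: one-sided n = 26 (power 0.812), which matches; two-sided n = 33, with power 0.705 at n = 26. Sidedness is not stated in the protocol; that is a separate matter.
- With all 40 planned participants, power is 0.882 two-sided or 0.936 one-sided.

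So 26 is a genuine calculation, but for voiding efficiency. The protocol gives no mean, SD or effect size for any of the six listed parameters, so power for Outcome 2A cannot be computed.

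**Step 4: check whether the procedure yields voiding efficiency.** The measure needs a voided volume and a residual volume. The Urodynamics section describes filling, prefilling and stimulation, but no voiding phase and no residual measurement. Stimulation also ends when urine leaks. How a voided fraction under stimulation would be obtained is therefore not described.

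**Step 5: check what the procedure already yields.** Pves is an Outcome 2A quantity, abdominal pressure is measured, and pelvic-floor EMG is recorded. Detrusor pressure is Pves minus abdominal pressure. Detrusor pressure change and pelvic-floor activity during contraction can therefore be derived without a new procedure, provided these recordings continue through the stimulation run. The protocol calls that run UDS as well, so this is a reasonable assumption.

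**The case against.** The strongest reply is that the data to examine the voiding question largely exist. Pressures and pelvic-floor EMG are recorded, the background review presents EMG as part of the assessment, and the analysis sentence speaks of UDS parameters without restricting them to the six. This stands as far as it goes. A reader might infer that the trial cannot address voiding at all, and the protocol does not support that: what is missing is a named outcome and, for voiding efficiency, a described measurement. The reply does not remove the mismatch, because the protocol itself fixes the outcome list.

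It can also be said that pressure at leakage partly reflects outlet resistance. Even so, it does not show coordinated sphincter relaxation or absence of DSD, and the protocol itself classes it under capacity/compliance.

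Three further inferences are tempting and should be resisted.

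- That adding voiding efficiency is a matter of wording, because voided and residual volumes are read at the same session. No section says that they are.
- That some storage volumes cannot be obtained in the stimulation run because it starts from a prefilled bladder. The text does not say whether filling continues. Fullness is among the events that end stimulation, which is compatible with continued filling, and the short stimulation periods are said to serve optimisation of the configuration. This is an ambiguity to resolve.
- That testing six parameters at 0.05 gives a calculable false-positive risk. The six are volume/pressure pairs from the same participants, so independence is implausible, and handling of multiplicity may sit in an analysis plan that is not shown.

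**Conclusion.** The point holds as an inconsistency within the protocol. None of the six Outcome 2A parameters measures voiding or sphincter relaxation, which make up one of the two halves of Objective and Hypothesis 2A. The minimum of 26 reproduces for voiding efficiency, as a one-sided paired t-test, and applies to none of the six parameters; their power is unknown. Voiding efficiency is not a listed outcome or analysis variable and has no described measurement.

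The conclusion rests on the wording of the protocol and does not depend on the power arithmetic. It does not mean that the trial is too small, and no corrected sample size follows from it. For a proof-of-concept study this should be put right, and doing so does not require the design to be rebuilt.

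**What to change.** 1. **Add two measures to Outcome 2A from signals already recorded:** change in detrusor pressure (Pves minus abdominal pressure), and pelvic-floor EMG activity during detrusor contraction, each with stimulation on versus off. State which period supplies the stimulation-off value. The EMG comes from a surface electrode on the perineum, so describe it as a proxy for the urethral sphincter. Cost: protocol wording and some extra signal analysis.

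2. **Settle voiding efficiency in one of two ways.** (a) List it as an outcome and state in the Urodynamics section how voided and residual volumes are obtained, reconciled with the text that ends stimulation at urine leakage. This adds a measurement step, so it costs more than wording. (b) State in the Statistical Plan that the power figure does not apply to the listed Outcome 2A parameters, and limit the voiding claim in Hypothesis 2A to what the listed outcomes measure. This costs wording only.

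3. **Clarify the stimulation run.** Say in the Urodynamics section whether filling continues after the 50-75% prefill, so that it is clear which storage volumes the run yields for comparison with baseline. Cost: one sentence.

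### Outcome 2A has no measure of emptying and no direction of success, so the hypothesised voiding benefit cannot be shown and an induced void could be recorded as a loss of bladder volume

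*Protocol*

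**What the plan says.** Under Objectives, Hypotheses and Outcomes, Objective 2A sets two targets. The first is that TCSCS "can induce detrusor contractions (*voiding function*) while relaxing the EUS". The second, described as independent of the first, is higher sphincter tone for storage; the wording that joins the two is "while relaxing the EUS, i.e. to avoid DSD and independently enhance EUS tone". Hypothesis 2A claims both: "short-term TCSCS will improve voiding and storage functions without ACVEs".

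Outcome 2A is introduced as "Changes from baseline in the following UDS parameters for bladder capacity/compliance". Six items follow: volume and pressure at first sensation, at the leakage point and at maximum bladder volume. No voided volume, post-void residual, voiding efficiency or sphincter activity is listed, and no item has a direction of success.

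The Urodynamics section describes the stimulated test once: "we will first prefill the bladder (i.e. 50-75% of cystometric capacity from the first UDS"), then stimulation blocks of 60 s "interspersed with 30 s rest (i.e. no stim) to optimize the configuration for each individual". Stimulation ends at a sensation of fullness, at urine leakage, at a blood-pressure limit or on request. No configuration is marked as serving voiding or storage.

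The Statistical Plan derives the minimum sample of 26 from a change in voiding efficiency. It analyses the short-term urodynamic parameters "with or without different stimulation configurations will be assessed using a repeated measures non-parametric analysis of variance (ANOVA"), with the Kruskal-Wallis test named.

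**The concern.** The hypothesis has two halves and the outcome list can register only one. If stimulation empties the bladder with a relaxed sphincter, which is the first target, no listed parameter records a success.

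The listed parameters may also move the wrong way. Emptying at or near the prefill ends the run at a volume below baseline capacity, with intravesical pressure raised by the contraction. A storage response moves the volumes up. Both are improvements under Hypothesis 2A, yet the leakage and maximum volumes shift in opposite directions, and the protocol gives no rule for telling an induced void from a leak. At stake is whether the trial can answer the voiding half of its own hypothesis, and whether the storage half can be read cleanly.

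**Working it through.** **1. The plan's own sample size.** Inputs from the Statistical Plan: voiding efficiency 37.8 (SD 40.6)% off and 58.2 (SD 39.4)% on, effect size 0.510, power 0.8, alpha 0.05.

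- Effect size: (58.2 − 37.8) / ((40.6 + 39.4)/2) = 20.4 / 40.0 = 0.510. This matches.
- Used as a standardised paired difference, which implies a within-person correlation of about 0.5, a one-sided paired t-test needs N = 26 (power 0.812). This matches. A two-sided test would need 33; the plan does not state sidedness.

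So 26 is a valid figure for voiding efficiency. It gives no power for any of the six parameters in Outcome 2A.

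**2. What the outcome list can register.**

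| Target in Objective 2A | Listed measure that could show success | Likely movement of the listed parameters |
|---|---|---|
| Voiding: contraction with relaxed sphincter | None | Leakage/maximum volume down, pressure up |
| Storage: higher sphincter tone | Volumes and pressures | Leakage/maximum volume up |

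First-sensation volume and pressure may be unaffected if sensation precedes emptying.

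**3. Size of the possible misrecording.** If a void occurs at the prefill and its volume is entered as the leakage or maximum volume, the recorded loss is L = 1 − prefill:

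- prefill 50%: L = 50%
- prefill 75%: L = 25%

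The prefill is the protocol's figure. Entering the void this way is an assumption, because no rule is given.

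**4. When the two responses offset each other.** Assume one stimulation-on value per participant, a share v who void, and a storage gain g in the rest. The mean change is (1 − v)g − vL, which is zero at v = g/(g + L).

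| Assumed gain g | v at 50% prefill | v at 75% prefill |
|---|---|---|
| 10% | 0.10/0.60 = 17% | 0.10/0.35 = 29% |
| 20% | 0.20/0.70 = 29% | 0.20/0.45 = 44% |
| 30% | 0.30/0.80 = 38% | 0.30/0.55 = 55% |

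The protocol gives neither v nor g.

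**5. Dependence on how the conditions are coded.** Simulation with N = 40, SD of the on/off change 25% of capacity, storage gain 20%, and voiders losing 25-50%:

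- One stimulation-on condition, two-sided signed-rank test: power to show a gain is about 100% with no voiders, about 0.40 with 20% voiders and about 0.09 with 30%.
- Off, storage setting and voiding setting as three conditions, each participant responding to one setting only, Friedman test: power is about 0.97 or higher at 20%, 30% and 50% voiders.

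The same responses are nearly invisible or readily detected depending on a coding choice that the protocol does not state. The omnibus test does not by itself say which direction is an improvement.

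**The case against.** A reader might go further and infer that voiding and storage runs are pooled, so that a real voiding effect will cancel the storage gain and be reported as deterioration. The documents do not support that. The Urodynamics section describes repeated blocks, the Statistical Plan speaks of different configurations, and Objective 2A calls the storage effect independent. The protocol does not say that the settings are mixed. The low power figures apply to a two-condition signed-rank test, whereas the Statistical Plan assigns signed-rank tests to the long-term urodynamic comparison and a repeated-measures non-parametric ANOVA to the short-term one. With separate conditions, opposite shifts add to the omnibus signal. Nor does any rule say that a fall in volume counts as harm. Three of the six parameters are pressures, and first-sensation values may be untouched. All of this stands, and it limits the point to what could happen.

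The protocol does not say that the settings are kept apart either. It optimises a configuration for each individual, so a configuration need not mean the same thing across participants.

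It may also be said that such detail belongs in a statistical analysis plan, which is not shown. A label for each configuration could indeed sit there. The objective, the outcome list and the test procedure are protocol content, and the mismatch lies between them.

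**Conclusion.** The point holds in a limited form. Three things are firm from the text: Hypothesis 2A claims a voiding benefit that Outcome 2A cannot show; the sample size rests on a variable missing from that outcome list; and no parameter has a direction of success.

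It is conditional that an induced void would be recorded as a leakage or maximum volume about 25-50% below baseline. This assumes emptying at the prefill and no rule separating a void from a leak. Offsetting of storage gains is conditional again on analysing both kinds of response under one stimulation-on condition. Its size depends on the share of voiders, the storage gain and the variability, none of which the protocol gives, so no power loss can be attributed to the plan. For a proof-of-concept study this should be corrected, but it does not invalidate the design.

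**What to change.** - Add voiding efficiency, from voided and post-void residual volume, as the voiding outcome of 2A. This also aligns the outcome with the sample-size calculation.
- State the direction of improvement for each of the six storage parameters.
- Classify a detrusor contraction with emptying during stimulation as a voiding result, not as a leakage-point or maximum-volume result.
- In the Statistical Plan, keep voiding-target and storage-target configurations as separate conditions, each compared with stimulation off on its own outcomes.
- Assign the target by a pre-stated rule that does not depend on the analysed run, for example set during the optimisation in UDS 1 and tested in UDS 2. Labelling from the Visit 3 mapping alone is doubtful: it records muscle responses rather than bladder pressure, and the stimulated urodynamics are themselves used to find the configuration.
- Reconcile the stimulation and stopping text in the Urodynamics section with the two targets of Objective 2A. No clinical rule is proposed here.

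The cost is protocol wording, recording of voided and residual volume, and a label on configurations already planned. The downside is fewer runs per comparison.
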